## Discussion

In this multicenter, observational, retrospective registry, we aim of investigate the long-term cardiovascular implications of COVID-19. Currently is known that the presence of myocardial injury, vascular dysfunction and thrombosis in patients with COVID-19 have an important role in the short-term prognosis in these patients [9]. Previous experience with the severe acute respiratory syndrome coronavirus-1 (SARS-CoV-1) emerged in 2002, suggests that both the underlying disease and its treatment could be associated with a worse cardiovascular prognosis. In a study of 25 survivors of SARS-CoV-1, at 12 years of follow-up, altered lipid metabolism was found [17]. Similarly, viral diseases such as influenza A are associated with increased cardiovascular mortality after infection [18].

The focus of this registry will be on the cardiovascular outcomes, providing data not only about cardiac ischemic events but also arrhythmias, cerebrovascular events and heart failure. It should be highlighted that our findings will be applicable to any COVID19 patient, regardless of the severity of the disease, as we will be including a consecutive population of patients with COVID-19 infection. Confirmed cases will be evaluated and compared with those patients who did not have COVID-19 infection. This approach will offer a greater security at the moment of assessing study’s findings. This control group will help to minimize bias that would arise if only COVID-19 patients were independently analyzed. Cox regression will help to distinguish the independent predictors for mortality among the patients of the study. However, considering that a proportion of the SARS-CoV-2 infections can be asymptomatic, there can be a degree of bias if the control patients (non-COVID-19 group) become infected but exhibit an asymptomatic disease during follow-up. Nevertheless, potential patients fulfilling these characteristics can represent a minimal part of the sample size.

It is important to mention as strength of the study, that the events will be adjudicated by an independent committee blinded to the patients’ treatment allocation and trial results. This will guarantee a better evaluation of the study events.

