### Patient selection

Inclusion criteria are:

At least 18 years of age.Patient who underwent a nasopharyngeal swab for real-time reverse transcriptase-polymerase chain reaction (RT-PCR) for SARS-CoV2 between March 2020 and August 2020.

Exclusion criteria are:

Those with terminal diseases and a life expectancy <1 year before the diagnosis will be excluded.

Patients will be classified into two groups: patients with confirmed COVID-19 (positive RT-PCRT for SARS-CoV-2) and patients without COVID-19 (negative RT-PCR for SARS-CoV2, and absence of absence of suspicious symptoms).

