Demographic data • Age • Sex Risk factors and baseline comorbidities • Hypertension • Diabetes mellitus • Hypercholesterolemia • Smoking status • Kidney chronic disease • Previous ACS • Previous Stroke • Heart failure • Atrial fibrillation • Previous PE and DVT • Cancer • Organ transplant • Immunosupresion • Frailty Charlson Comorbidity Index Baseline medication • Anti-hypertensive drugs and cardiovascular medication • Chronic anticoagulation • Oral hypoglycemic agents • Insulin • Proton pump inhibitors • NSAIDs	Symptoms Hospitalization • Length of stay Drugs: • Anti-hypertensive drugs and cardiovascular medication. • Anticoagulation • Antivirals • Immunosuppressive drugs • Vasopressors • ICU admission • Invasive mechanical ventilation Biomarkers • Hemoglobin* • Lymphocytes* • Platelets* • Creatinine** • HscTnI** • NT-proBNP** • D-dimer** • Fibrinogen* • Prothrombin time** In-hospital events: • All-cause death • Cardiovascular death • ACS • Stroke • DVT and PE • Cardiac arrhytmias • Bleeding • Red blood cell transfusion Discharge medication	New SARS-CoV-2 infection Vaccination against SARS-CoV-2 Outcomes • All cause death • Cardiovascular death • ACS • Stroke • Heart failure hospitalization • PE • Cardiac arrhytmias

ACS, acute coronary syndrome; DVT, deep venous thrombosis; Hs-cTnI, high sensitivity cardiac troponin I; NSAIDs, non-steroidal anti-inflammatory drugs; PE, pulmonary embolism.

*Lowest values during hospitalization.

*Highest values during hospitalization.

All the data will be obtained from electronic records (medical history). If deemed necessary, the investigator may check the patient vital status in the social national security database.

Clinical follow-up will be performed at 1-year. The flowchart and study timeline are detailed in **Fig 1**.

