### Statistical analysis plan

We did not estimate a precise sample size, due to lack of literature reports and we aim to get the maximum numbers of patients possible.

Continuous variables will be presented as mean ± standard deviation. Categorical variables will be reported as absolute number and percentage. Differences in proportions will be tested with Chi-square test or Fishers exact test and differences in continuous variables will be tested with a Student’s t-test. Kaplan-Meier method will be used to derive the event rates at follow-up and to plot time-to-event curves. Patients not eligible for 1-year follow-up will be considered at risk until the date of last contact, at which point they will be censored.

To determine the predictors of cardiovascular death, a Cox proportional hazards model will be used together with the Wald test to compare the results between the groups (patients with positive vs. negative RT-PCR for SARS-CoV-2).

All p-values will be two-sided and a value <0.05 will be considered statistically significant. All data will be processed using the Statistical Package for Social Sciences, version 22 (SPSS Inc., Chicago, IL, USA).

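### The primary Cox comparison gives no role to recorded new SARS-CoV-2 infection in controls, and the only infection bias the Discussion considers is set aside without a figure

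*Protocol article*

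**What the plan says.** - **Groups.** Patient selection assigns patients by swab result: "Patients will be classified into two groups: patients with confirmed COVID-19 (positive RT-PCRT for SARS-CoV-2) and patients without COVID-19". The second group needs a negative RT-PCR and no suspicious symptoms. The swab window is March to August 2020.
- **Follow-up.** Data capture states: "Clinical follow-up will be performed at 1-year". The Fig 1 legend places the outcome analysis in August 2021. All data come from electronic records.
- **Infection after the index swab.** The long-term column of Table 2 lists "New SARS-CoV-2 infection" as an item to be collected.
- **Analysis.** The Statistical analysis plan section names a Cox model with a Wald test for "patients with positive vs. negative RT-PCR for SARS-CoV-2". Its only censoring rule is the date of last contact. It mentions no time-dependent exposure and no use of the new-infection item.
- **Stated limitation.** The Discussion accepts that "there can be a degree of bias if the control patients (non-COVID-19 group) become infected but exhibit an asymptomatic disease during follow-up", and then says that "potential patients fulfilling these characteristics can represent a minimal part of the sample size".

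**The concern.** Controls are followed for a year while the pandemic continues. Some may be infected in that time, and the protocol expects this, because it collects the item. If these patients remain in the negative group, any cardiovascular death that follows their infection is counted as an event in an unexposed patient. The contrast then differs from the one the Discussion describes, which is with patients who did not have the infection.

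The Discussion covers only part of this. It names infection without symptoms, which a records-based registry would often miss. Diagnosed infection in controls, which the registry can record and the analysis could use, is not mentioned.

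The primary comparison is at stake. Attenuation would understate an association with cardiovascular death and reduce the power to detect it.

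**Working it through.** **What the documents supply.** The protocol article gives no sample size, effect size, power or infection rate, so there is no figure to reproduce. It does give two-sided testing at 0.05. All other inputs below are assumptions.

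**Formula.** Let h be the cardiovascular death hazard in uninfected controls and HR the true ratio for infected versus uninfected. Let p be the share of control risk time that carries the infected hazard. The average control hazard is h[(1 − p) + p·HR] = h[1 + p(HR − 1)], so

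observed HR = HR / [1 + p(HR − 1)].

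**Full hazard in infected controls** (example: HR 2.0, p = 10% gives 2.0/1.10 = 1.82):

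| True HR | p = 5% | p = 10% | p = 20% |
|---|---|---|---|
| 1.5 | 1.46 | 1.43 | 1.36 |
| 2.0 | 1.90 | 1.82 | 1.67 |
| 3.0 | 2.73 | 2.50 | 2.14 |

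At p = 2%, a true HR of 2.0 is observed as 2.0/1.02 = 1.96.

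**Partial hazard.** If infected controls carry half the log hazard ratio, their ratio is √2 = 1.414 when HR = 2.0. The observed value is 2.0/[1 + p(0.414)], which is 1.96, 1.92 and 1.85 at p = 5%, 10% and 20%. If their infections add no risk, the observed value stays at 2.0.

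**Power.** Schoenfeld's formula with an assumed 1:1 split, two-sided 0.05 and HR 2.0 needs 66 events for 80% power. With the same 66 events and the full-hazard dilution, power is about 75%, 68% and 55% at p = 5%, 10% and 20%. Restoring 80% would take 76, 88 and 121 events.

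**What the shares imply.** If infections fall evenly over the year, an infected control spends on average half the year infected, so p is about half the proportion infected. Shares of 5%, 10% and 20% then correspond to about 10%, 20% and 40% of controls infected. The documents do not say which is plausible. The formula also assumes a constant hazard after infection. If the excess is concentrated in the acute phase, a share of person-time is not the right measure.

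**The case against.** The strongest reply is that the protocol article does not say what happens to controls with a recorded infection. A fuller analysis plan, not shown, may contain a rule, and collecting the item suggests that the investigators foresaw the problem. Comparison by index status is also a legitimate baseline contrast, with error expected toward the null.

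This stands in part. A reader might infer that the protocol states that such controls remain in the negative group. It does not: this follows from reading Patient selection, the Statistical analysis plan section and the Discussion together. But the article does fix the comparison and its only censoring rule, and the Discussion takes up control infection and closes it with an unsupported judgement of size. That goes beyond missing detail.

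Second, the sentence on size concerns only infection without symptoms. A reader might take it as dismissing all control infection, or expect a count of recorded infections to replace it. Neither is right: recorded and undetected infections are different quantities.

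Third, a time-dependent analysis has its own biases. A control admitted with a cardiovascular event may be tested because of that admission, so the event could trigger the switch in exposure. Censoring at infection may be informative. Both objections are sound. They limit the remedy to sensitivity analyses but do not remove the need for one.

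**Conclusion.** The point holds as a gap in how the primary comparison treats infected control time. With groups set by RT-PCR result, censoring only at last contact and no role for the new-infection item, the plan as written counts infected control time as uninfected. Attenuation of the primary hazard ratio toward 1 is then expected, provided that infection raises cardiovascular mortality.

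A reader might go further and conclude that the effect is diluted, or substantially so. The documents do not support that. Under the assumed shares the loss is slight at a few percent of control risk time. It is material at 10% to 20% with full hazard, where a true 2.0 reads as 1.82 to 1.67, and zero if the infections add no risk. Nor do the documents show which infections lead to cardiovascular death. The judgement that undetected infections are few is equally without support, since no infection rate is given.

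**What to change.** 1. Keep the RT-PCR group comparison as primary. State that the index date is the first swab in the window, so that a negative swab followed by a positive one within March to August 2020 is handled in the same way at every center. A patient should not be classed as positive from a date before the positive test, because that would credit the positive group with time in which the patient had to survive to be tested again.
2. Pre-specify one sensitivity Cox model of cardiovascular death with infection as a time-dependent exposure, in which controls change status on the date of their first recorded positive test. Show a version in which a positive test found at the event admission does not count as prior exposure.
3. Alongside it, show the result with controls censored at that date, and note that this censoring may be informative.
4. Report the number of controls with a recorded new infection.
5. In the Discussion, keep undetected asymptomatic infection as a limitation, remove the claim about its size, and say how diagnosed infection in controls is handled.

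The cost is a few sentences, one additional model with its variants, and a count. The item is already in Table 2, but the date of infection must be available. If it is not recorded, it has to be retrieved from the electronic records for the controls concerned. Undetected infections stay outside the reach of these analyses.

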## Conclusion

The results of the CV COVID-19 registry will contribute to a better understanding of the short and long-term implications of this disease. It will provide information about cardiovascular mortality and cardiac events at one year of follow-up. Also, it will identify characteristics associated with higher incidence of complications, defining a profile of COVID-19 patients with worse prognosis.
